As per the surgical protocol, all patients will also undergo tenotomy of the long head of biceps and acromioplasty with excision of the coracoacromial ligament. Also, excision of the acromioclavicular joint will be performed only if patients complain of pain in that region along with degenerative changes being shown on X-rays, or found intraoperatively. If any further lesions are detected during the operation, the surgeon will proceed to repair them and such incidents will also be recorded. Skin closure will be performed with 3.0 nylon sutures. Nonadhesive dressings and pressure dressings will be applied to the top of the shoulder and patients will be placed in a 30^o^ abduction sling immediately after completion of surgery.

Patients will stay overnight at the hospital. Physiotherapists will advise them as per the physiotherapeutic protocol (Table 2). The abduction sling will remain for the first 6 weeks. Sutures will be removed 10 days after surgery. Outpatient and physiotherapy clinic follow-up will be arranged at 6 weeks, 3 months, and 6 and 12 months postoperatively. Neurology clinics for NC/EMG studies will be arranged at 6 and 12 months postoperatively. Outcome scores will be collected at 6 and 12 months after surgery.

**Table 2 Tab2:** Brief physiotherapy protocol for postoperative rehabilitation of repaired large/massive rotator cuff tears

Time	Focus	Range of motion	Recommended exercises	Precautions
0–6 weeks	Tissue healing	No passive assisted or active ROM of shoulder allowed apart from table slides	• Restricted table slides after 2nd week to 30° • AROM of elbow, wrist, hand	• No active reaching • Sling at all times
6–12 weeks	PROM, AAROM with transition to AROM	Regain full PROM and AAROM, transition to AROM at 10 weeks	• PROM of shoulder, pendulums, scapular mobility, ball squeeze begin AAROM at 8 weeks • Isometrics and active progression at 10 weeks	• No resisted activity and lifting • Avoid overloading of supraspinatus • Must regain scapular rhythm before transition to strengthening
12–24 weeks	AROM and progressive strengthening	Regain full AROM	• Continue PROM and AAROM as needed • Initiate strengthening and progress AROM to functional planes • Progress proprioceptive drills, rhythmic stabilization, push-ups, resistance band	• No heavy or repetitive overhead activities • Limited return to gym after 20th week if AROM with satisfactory scapular rhythm has been achieved • Free full ROM

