#### Randomization/blinding

The choice of resecting or not the transverse scapular ligament will be done in a randomized manner. Randomization will be made by using the Microsoft Office Excel program and its RAND function. Forty-two cells will be created and the numbers in them will be rounded up so that they have no decimals. Odd numbers will create the first group and even numbers will create the second group. If RAND function fails to create even groups, it will be redone until even groups of odd and even numbers are achieved. Patients will be placed at each consecutive cell at the time of recruitment, after inclusion in this trial, and will be randomized by the statistician. The surgeon will be informed about the type of treatment needed for patients on the admission day. This will be facilitated with opaque envelopes containing the patient’s group, which the primary investigator will have received from the statistician. The primary investigator will place this envelope inside the patient’s physical records just before the patient is taken to the operating room. An operating department practitioner nurse will open the envelope just after the surgeon finishes the rotator cuff repair and will instruct him, according to the patient’s group, whether to release the ligament or not. By doing this, the surgeon will not be biased by knowing the patient’s group before repairing the cuff (avoidance of performance bias).

The surgeon, therefore, clearly cannot be blinded to the type of procedure, but this will not bring any bias to the study. Patients, physiotherapists, and the clinician measuring outcomes will be blinded to each patient’s allocated treatment. The neurologist will also not know the type of surgery performed. This blinding will assist in obtaining objective results while performing NC/EMG studies and should exclude such bias.

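### Opening the envelope just after the cuff repair protects only that repair: judgements on further lesions, and in part on the acromioclavicular joint, may follow with the arm known

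*Protocol article*

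**What the plan says.** Randomization/blinding sets the moment of disclosure: "An operating department practitioner nurse will open the envelope just after the surgeon finishes the rotator cuff repair". The nurse then tells the surgeon whether to release the ligament. The stated gain is that the surgeon does not know the group "before repairing the cuff (avoidance of performance bias"). The next paragraph goes further: "The surgeon, therefore, clearly cannot be blinded to the type of procedure, but this will not bring any bias to the study".

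Study procedure describes the other surgery in three parts:

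- Fixed for everyone: "all patients will also undergo tenotomy of the long head of biceps and acromioplasty with excision of the coracoacromial ligament".
- Conditional: "excision of the acromioclavicular joint will be performed only if patients complain of pain in that region". The joint must also show degeneration, either on radiographs or at surgery.
- Unplanned: "If any further lesions are detected during the operation, the surgeon will proceed to repair them and such incidents will also be recorded".

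Neither section says whether the conditional and unplanned steps are decided before or after the envelope is opened.

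**The concern.** The comparison is meant to isolate ligament release. Holding back the arm until the cuff is repaired is a good device for that, because the main shared procedure is then done without knowledge of the group. The protection ends when the envelope is opened. Any judgement the surgeon still has to make afterwards, such as whether an appearance counts as a lesion to be repaired, is made with the arm known.

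If those judgements differed by arm, the groups would differ in the surgery received and not only in the release. Blinding the patients and assessors would not remove that difference, because it lies in the treatment and not in the measurement. The flat statement that the surgeon brings no bias would then claim more than the design delivers.

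**Working it through.** The point contains no figure, so the check is a comparison of the two sections. The sample size is not affected. It reproduces: with full recovery of 100% against 66.67%, Fisher's exact test has power 0.812 at 19 per group and 0.769 at 18, which gives the stated 38.

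**Step 1. When is the arm known?** By the envelope account in Randomization/blinding, at the end of the cuff repair.

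**Step 2. Which parts of the operation can depend on that knowledge?**

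| Step | Who receives it | Placed before disclosure? | Room for judgement once the arm is known |
|---|---|---|---|
| Cuff repair | All | Yes | None, on the envelope account |
| Biceps tenotomy, acromioplasty | All | Not stated | Little, since it is required in both arms |
| Acromioclavicular excision | Pain there plus degenerative change, on X-ray or at surgery | Not stated | Limited to degeneration judged at surgery, in patients with pain |
| Repair of further lesions | Whoever has one detected | Not stated | What is looked for and what counts as a lesion |
| Ligament release | Release arm | After, by design | This is the intervention |

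Two rows remain open: further lesions, and in part the acromioclavicular joint.

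**Step 3. Which outcomes could be touched?** Trial objectives/endpoints makes suprascapular nerve function on nerve conduction and electromyography the primary endpoint. One neurologist performs all these studies, blinded to the surgery. An extra repair elsewhere in the shoulder is unlikely to move those readings much. The same section also has clinical signs of full recovery compared before and after surgery. The section on preoperative and postoperative examinations describes a Constant-Murley score that includes pain, function, range of motion and strength, and an ASES score with 50 of its 100 points for pain. Treating a painful joint or another lesion could plausibly shift these.

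**Step 4. Can the effect be sized?** No. The document gives no frequency for either procedure, no effect on any score, and no reason to expect the shift to favour one arm.

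**Step 5. Is the disclosure point itself secure?** Not on the text. Study procedure says that the operating surgeon, alone, is aware of the randomization results and the allocation list. Randomization/blinding also says that the surgeon is told the treatment on the admission day. The second statement may only describe the envelope in loose terms, since the envelopes are introduced in the next sentence. The first is harder to square with a surgeon who learns the arm after the repair. If either applies as written, the arm is known throughout the operation, and the cuff repair is exposed as well.

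**The case against.** The strongest reply is that this rests on silence. The order of operative steps belongs in a surgical protocol, which the article mentions but which is not shown, and these steps may well come before the repair. That is fair as to sequence. But the article itself fixes the disclosure point and itself makes the categorical no-bias statement, and the first does not support the second.

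Other objections stand and limit the point:

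- A reader might infer that the surgeon has free discretion over acromioclavicular excision. The text does not support that. A pain complaint is required, it comes from the patient, and on the natural reading the intraoperative route concerns only where the degeneration is seen.
- The wording on further lesions is directive, and such repairs are recorded. Recording allows an imbalance to be described, though it does not prevent one.
- The explicit performance-bias claim covers only the cuff repair and, on the envelope account, is correct. The overstatement is in the broader sentence that follows it.
- The shoulder scores are not named as the primary, secondary or tertiary endpoint. Patients, physiotherapists and the outcome clinician are blinded.

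A reader might also infer that the arms will differ by some number of patients, or that the primary result is compromised. Any such number would be invented, and the blinded primary measurement argues against the second inference.

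**Conclusion.** The point holds as a minor weakness of design and wording. The stated timing protects the cuff repair. It does not protect judgements on further lesions, or on acromioclavicular degeneration seen at surgery in patients with pain there. The sentence that the unblinded surgeon brings no bias is therefore broader than the safeguard.

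The likely effect is small on the primary nerve endpoint and more plausible on the shoulder scores and clinical signs. Size and direction are unknown.

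This rests on two assumptions: that the envelope account is the operative one, and that at least some of these judgements are made after the repair. The document does not settle either. The text shows that arm-dependent choices are possible; it does not show that they will occur.

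**What to change.** In Randomization/blinding, have the envelope opened only when the cuff repair is finished **and** the surgeon has recorded the intraoperative findings and the decision on every other procedure. Record any procedure added after opening with its reason and its timing. This should not be logged as a deviation, because Study procedure directs the surgeon to repair such lesions. Tabulate concomitant procedures by arm in the report.

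Limit the no-bias sentence to what the envelope timing protects.

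The change works only if the surgeon does not already know the arm. The envelope procedure must therefore be reconciled with the statement in Study procedure about the allocation list and with the admission-day sentence in Randomization/blinding.

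The cost is one form entry before the envelope is opened. No staff, indication, procedure or sample size changes.

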### Procedure risks/complications

Releasing the superior transverse scapular ligament carries the risk of damage to the SSN and artery. Normally, the nerve lies inferior to the ligament and medially is protected by the shaver during soft-tissue resection. The artery, however, passes superior to the ligament and is potentially in jeopardy. Care will be taken not to cut the artery. However, if it is injured, coagulation may be achieved by using a radiofrequency device. No additional morbidity has been observed in such cases due to the rich collateral circulation of this region. Patients will be informed of these risks before signing the Consent Form.

### Trial duration

The main trial period will start 6 weeks prior to surgery (where clinical NC/EMG and MRI evaluation will be done) and will include the operative intervention and the postoperative period up to the last follow-up. Follow-up clinical examinations and NC/EMG studies for all patients will be conducted at 6 and 12 months after surgery. MRI studies for each patient will be done at least 1 year after the date of the operation.

With a recruitment period of 24 months and a follow-up period of 12 months, the total length of this study is expected to be approximately 36 months. This trial will end when all the necessary 42 patients have completed it. Also, the principal investigators may decide to terminate the study at any time for any reasonable or medical reasons. The final report of this trial will follow the CONSORT guidelines and its extension for nonpharmacological interventions.

### Statistics

#### Sample size calculation

Statistical analysis of previous relevant medical literature was used in order to identify the number of patients needed for this trial. Since no similar studies could be found, we searched for results from similar articles relative to the trial. Costouros et al. [7] treated six patients with massive rotator cuff tears and SSN neuropathy by arthroscopically repairing the cuff. They found complete nerve recovery in four out of six patients. Oizumi et al. [17] performed an arthroscopic release in 18 patients with a rotator cuff tear and all had complete recovery from SSN palsy, although the diagnosis was clinical and no NC/EMG studies were done. Lafosse et al. [1] mention unpublished data of 29 massive rotator cuff tear cases accompanied by SSN neuropathy, where no statistical difference was found between patients who underwent nerve release and patients who did not; however, no further data or tables are provided and the cases are anecdotal. Therefore, we considered that 100% of patients undergoing nerve release and 66.67% of patients undergoing rotator cuff repair only could have full nerve recovery.

We used the statistical program G*Power [18] in order to do a priori power analysis of the primary endpoint of this study. By using a Fisher’s exact test to compute differences between these groups, a 100% success probability of the first group (nerve release) and a 66.67% probability of the second group, a error probability set at 0.05, power set at 0.8, and an allocation ratio equal to 1, a total of 38 patients were found to be needed, 19 for each group. Usually, patients who undergo such operations rarely miss standard follow-ups in this institution because these are part of their physiotherapy and clinical postoperative care (apart from the NC/EMG studies). If 10% of recruited patients fail to attend follow-ups for any reason, then 42 patients will be required for this RCT.

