### Trial objectives/endpoints

The primary endpoint of this study will be recording of changes of function of the SSN, as assessed by electromyography (EMG) and/or nerve conduction (NC) studies, preoperatively, and at 6 and 12 months postoperatively. All NC/EMG studies, pre and postoperative, will be performed by one neurologist for all included patients. Clinical signs of full recovery will also be assessed and compared pre and postoperatively.

Abnormal function of the SSN in EMG studies will be indicated by fibrillation and high-frequency discharge potentials. An abnormal NC assessment finding is defined according to the following values: infraspinatus latency >4.5 ms and an amplitude <8 mV from peak to peak and supraspinatus muscle latency >3.5 ms and an amplitude <8 mV from peak to peak [12]. The contralateral nerve will also be examined. Abnormal findings are also indicated when the difference in amplitude compared to the healthy side is more than 50%. According to patients’ results, the NC/EMG studies postoperatively will show full recovery of the nerve if all parameters are normal and partial recovery if the tested parameters are improved but not normalized. It is possible, due to some patients’ habitus and size, that NC studies may not be feasible to perform on these patients. In these cases, diagnosis will be established by EMG studies.

The secondary endpoint will be analyzing for possible correlations between tear size, SSN neuropathy frequency, and degree of postoperative nerve recovery. The diameter of the tear will be measured preoperatively with a ruler by using standardized MRI sagittal images. Measurement starts at the insertion of the tendon into the major tuberosity and ends at the most lateral margin of the torn rotator cuff. Only the largest measured diameter of the tear as found on images will be recorded.

The tertiary endpoint will be analyzing the rotator cuff muscles for changes of fatty infiltration as assessed using MRI studies (according to Goutallier’s classification) before and 12 months after the operation [13]. Goutallier classified fatty infiltration as: stage 0, normal muscle; stage 1, some fatty streaks; stage 2, less than 50% fatty muscle atrophy; stage 3, 50% fatty muscle atrophy; stage 4, greater than 50% fatty muscle atrophy.

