The technique of arthroscopic transverse scapular ligament dissection has been described previously [1, 27–29]. Lafosse et al. in 2007 reported excellent outcomes in nine out of ten patients who underwent SSN arthroscopic decompression without rotator cuff repair [28]. Complete normalization of latency in NC/EMG studies was found in seven of these patients. Costouros et al. reported six patients with SSN neuropathy related to massive cuff tear. He found complete improvement in EMG function in four and partial recovery in two patients [7]. In a study by Shah et al., 21/24 (87.5%) patients had deep posterior shoulder pain and NC/EMG findings of SSN denervation. After SSN decompression, 17/24 (71%) of these patients had reduced levels of pain at 9 weeks after surgery and demonstrated improved ASES scores [30]. The authors also hypothesized that there may be a subgroup of patients with negative NC/EMG studies presenting with unexplained posterior shoulder pain and that these patients may respond to SSN decompression.

The studies above show promising results after release of the SSN, but reversal of muscle atrophy is not always observed. Kim et al. reported 90% of patients with profound muscle weakness regaining supraspinatus muscle strength to grade 4 or better, but infraspinatus muscle strength gains were less predictable [11]. Fabre et al. reported 89% of patients obtaining good-to-excellent outcome after open SSN decompression, but reversal of muscle atrophy was only seen in half of these patients (52%) [31].

In conclusion, published studies so far deliver some evidence regarding the relation between SSN and massive cuff tears and suggest good/excellent postoperative outcomes, with or without releasing the SSN. These cohort studies provide ultimately inconsistent and ambivalent results, as they do not measure their current management with an alternate treatment. The need for comparable studies becomes apparent in order to create a guideline, which would assist shoulder surgeons in making effective and safe treatment choices when dealing with patients with repairable large/massive rotator cuff tears and SSN neuropathy.

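### The 80% power for the NC/EMG primary endpoint holds only at essentially 100% recovery after release, a rate taken from a series assessed without NC/EMG

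*Protocol article*

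**What the plan says.** Under Trial objectives/endpoints, the primary endpoint is change in suprascapular nerve function on EMG and/or NC studies. Postoperative studies show "full recovery of the nerve if all parameters are normal"; improvement short of that is partial recovery.

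The Sample size calculation section takes its two rates from different sources:

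- **Repair alone.** "They found complete nerve recovery in four out of six patients". The Discussion describes the same six patients in terms of EMG function.
- **Release.** In 18 patients, "all had complete recovery from SSN palsy, although the diagnosis was clinical and no NC/EMG studies were done".

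It concludes: "Therefore, we considered that 100% of patients undergoing nerve release and 66.67% of patients undergoing rotator cuff repair only could have full nerve recovery". It then applies Fisher's exact test to the primary endpoint with alpha 0.05, power 0.8 and equal allocation, arrives at 38 patients (19 per arm), and raises this to 42 for 10% loss to follow-up. Whether the test is one- or two-sided is not stated. No power is given for any other pair of rates.

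Two other items bear on the 100%. The Sample size calculation section mentions 29 unpublished cases in which "no statistical difference was found between patients who underwent nerve release and patients who did not", and calls them anecdotal. The Discussion reports a ten-patient series of arthroscopic decompression without cuff repair: "Complete normalization of latency in NC/EMG studies was found in seven of these patients".

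**The concern.** The planned difference of 33 percentage points subtracts an EMG-based rate from a clinically judged one. The trial's own endpoint requires every electrodiagnostic parameter to be normal, and nothing cited shows that all released nerves reach that standard.

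The choice matters because 100% is the most favourable value possible. The release arm then has no sampling variation, and any true rate below it costs power quickly.

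The Discussion says that if both operations have the same potential to reverse the neuropathy, release is unnecessary. A non-significant result is therefore likely to be read as a reason to omit release. A reader who trusts the 80% would give such a result more weight than the design can bear.

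**Working it through.** **Inputs.** From Sample size calculation: release 100%, repair alone 66.67% (4/6), alpha 0.05, power 0.80, 1:1 allocation, Fisher's exact test, 19 per arm. Two-sided testing is assumed. All other rates below are assumptions chosen to show the range.

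**Formula.** Power = sum over all tables (a, b) of Bin(a; 19, p_release) × Bin(b; 19, p_control) × [Fisher p ≤ 0.05].

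**1. Reproducing the 38.** With release at 100%, a is always 19.

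- Control 14/19: p = 2 × C(19,5)/C(38,5) = 2 × 11628/501942 = 0.046, significant.
- Control 15/19: p = 2 × C(19,4)/C(38,4) = 2 × 3876/73815 = 0.105, not significant.
- Power = P(Bin(19, 2/3) ≤ 14) = 0.812. At 18 per arm it is 0.769.

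So 19 per arm is correct. One-sided testing at 0.05 also gives 0.812 at 19 per arm.

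**2. What each unrecovered nerve in the release arm costs** (control 66.67%):

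| Release arm recovered | Significant if control is at most | Probability |
|---|---|---|
| 19/19 | 14/19 | 0.81 |
| 18/19 | 12/19 | 0.46 |
| 17/19 | 10/19 | 0.15 |

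**3. Release rate below 100%.** At 95%, the chances of 19, 18, 17 and 16 recoveries are 0.377, 0.377, 0.179 and 0.053. Then 0.377 × 0.812 + 0.377 × 0.457 + 0.179 × 0.146 + 0.053 × 0.065 ≈ 0.51. The full enumeration, with control at 66.67%, gives:

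| Release rate | Fisher, 19 per arm | Fisher, 21 per arm |
|---|---|---|
| 100% | 0.81 | 0.88 |
| 99% | 0.75 | 0.82 |
| 95% | 0.51 | 0.57 |
| 90% | 0.30 | 0.34 |

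Full retention of all 42 patients does not restore 80% at 95% or 90%. One-sided testing at 0.05 with 19 per arm gives 0.61 and 0.41 at those rates. For 80% power with two-sided Fisher, 33 per arm are needed at 95% and 55 at 90%.

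**4. Control rate other than 66.67%**, release at 100%, power = P(Bin(19, p) ≤ 14): 0.93 at p = 60% and 0.53 at p = 75% (0.5346 before rounding).

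**5. Sampling error in the sources.** Exact 95% intervals are 22% to 96% for 4/6 and 81% to 100% for 18/18. Even on its own clinical endpoint, the release series does not exclude rates well below 100%.

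**6. Boschloo's test at 19 per arm** (unconditional exact, Fisher's p as the statistic, two-sided 0.05). Its maximum size over a common recovery rate is 0.045, against 0.028 for Fisher. Power against 66.67% is 0.81, 0.61 and 0.40 at release rates of 100%, 95% and 90%. With 18/19 recovered it rejects at control 13/19 or fewer instead of 12/19. With 19/19 the cut-off stays at 14/19, so nothing changes at the planned alternative.

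**The case against.** The protocol is open about its sources. It says no similar studies could be found, states in the same paragraph that the 100% series had no NC/EMG, and says only that these rates could occur. The calculation is correct. All of this stands: the issue is an optimistic, disclosed planning assumption, not a concealed or arithmetical error. But disclosing the weakness did not change the power claim that follows from it.

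A reader might go further and infer that release normalizes only 7 of 10 nerves, so that the trial has almost no power. The documents do not support that. The count covers latency only and comes from decompression without cuff repair, whereas every patient here has a repair. The wording also leaves open whether the denominator is ten or the nine with excellent outcomes. Nor do the 29 cases establish a null effect, since the protocol gives no data for them. Both show only that 100% is not secure; neither is a planning rate.

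The uncertainty also runs both ways. A strict all-parameters criterion could lower the control rate too, and power is then higher (0.93 at 100% versus 60%). It would also overstate the case to say that a single unrecovered nerve removes most of the power: one takes it from 0.81 to 0.46, and two take it to 0.15.

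Finally, Fisher's test is valid and is named consistently in both statistical sections. Changing it is an improvement, not the correction of an error.

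**Conclusion.** The point holds in a limited form. The 38 is correctly computed, but the 80% is not supported for an NC/EMG endpoint, because its release rate comes from a clinically assessed series and the result holds only at essentially 100%. With control at 66.67% and two-sided Fisher at 19 per arm, power is about 51% at a 95% release rate and 30% at 90%. Those rates are illustrative; the documents give no release-arm NC/EMG rate for the combined procedure. It would go too far to say that the true power is known to be low, or that the sample size is wrong: a lower control rate would raise power, and none of the cited series fixes either rate for this endpoint.

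**What to change.** Keep 42 patients. In Sample size calculation, replace the single power claim with a conditional one, for example:

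> With 38 evaluable patients, Fisher's exact test (two-sided 0.05) has 81% power if full NC/EMG recovery is 100% with release and 66.7% with repair alone. The 100% comes from a series assessed clinically. With control at 66.7%, power is about 51% for a release rate of 95% and 30% for 90%. With release at 100%, it is about 93% if control is 60% and 53% if control is 75%. Rates other than 100% and 66.7% are illustrative.

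As a cheap improvement, before unblinding, pre-specify Boschloo's unconditional exact test (two-sided 0.05) in Statistical methods as the primary test, with Fisher's as sensitivity analysis. It respects the 0.05 level and loses nothing at the planned alternative, but recovers only part of the shortfall. The restated power is the essential change.

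The cost is an amendment to wording, a less favourable stated power, and a test less familiar to surgical readers. No patient, visit or measurement is added.
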